### Limitations, Risks, and Mitigation Strategies

At the same time, LLMs (and consequently conversational agents based on them) have several known limitations and risks. First, LLMs are trained on large human-authored textual corpora and thus can learn the biases and stereotypes expressed in these corpora. Training corpora may also make a conversational agent personalized to the users in a specific region or belonging to a particular culture or demographic group and thus less relatable and effective for other users. To mitigate this risk, the LLM underlying NAOMI will be fine-tuned on a large and diverse corpus of psychotherapy and MI counseling session transcripts.

The “black box” nature of LLMs is another source of potential risk since it translates into minimal control over what and understanding of how LLM-based conversational agents generate their responses. LLMs are also known to be prone to “hallucinations” [126], that is, generating outputs that are fluent and plausible, yet factually incorrect. The lack of interpretability and controllability is, however, common to many machine learning models and scientific understanding of the mechanism by which LLMs generate their output is still in its infancy [127]. The risk of NAOMI generating inappropriate or factually incorrect content will be mitigated by a study team member observing NAOMI’s interaction with every study participant and intervening should the interaction go awry.

Since study participants in each recruitment wave are not randomized to different conditions, our results may also be subject to cohort effects. Once NAOMI is fully developed and validated, we will address these limitations by conducting a randomized controlled trial testing NAOMI’s efficacy.

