### Goals of This Study

The main objectives of this study are 2-fold. The primary objective is to explore the feasibility of conducting unscripted weight loss MI with a fully automated LLM-based AI counselor by developing Neural Agent for Obesity Motivational Interviewing (NAOMI), a Web app for MI-style weight loss counseling. The secondary objectives are to test the acceptability and usability of NAOMI’s counseling and examine its ability to shift motivational precursors in a sample of overweight and obese patients recruited from primary health clinics.

Because this is a feasibility study involving a single interaction with NAOMI, it is not expected that participants will experience anthropometric changes. Participants will be advised to continue their current weight loss interventions (if any) and those who wish to engage in a weight loss intervention will be encouraged to contact their primary care provider for a referral to a weight loss treatment.

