### Study Hypotheses

This study will explore the following hypotheses: (1) NAOMI will achieve at least intermediate MI fidelity based on Motivational Interviewing Treatment Integrity (MITI) coding scheme [111] (see the Statistical Analysis subsection of the Methods section for more details); (2) At least 80% of the last cohort of study participants will find NAOMI acceptable and usable; specifically, they will like using NAOMI, be comfortable discussing their weight with it, find their interaction with it pleasant, its guidance helpful, and want to use it again (see the Measures subsection of the Methods section for more details); (3) Interaction with NAOMI will result in positive shifts in all motivational precursors (see the Qualitative Analysis subsection of the Methods section for more details).

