#### Study Visit

Participants will complete an in-person study visit using a tablet computer. If a study visit takes place online, the participants will complete the visit on a device of their choice using Zoom. The structure of the study visit is detailed in Textbox 1.

Structure of a study visit.Prior to the commencement of study visit activities, study staff will provide and review a copy of the study information sheet with eligible and interested patients and allow prospective participants to ask any questions. Prospective participants will be informed that by proceeding with study activities, they are consenting to participate in the study, however, their participation is completely voluntary and can stop at any time. Upon verbal acknowledgment from the prospective participant, study activities will proceed as follows:Study participants will complete the Participant Information Form and the Pre-Interaction Questionnaire (described below).Participants will then interact with Neural Agent for Obesity Motivational Interviewing (NAOMI) using a tablet computer (with a detachable keyboard) for at least 10 minutes but no more than 1 hour.Participants will complete the Post-Interaction Questionnaire, Usability Questionnaire, and the Consultation and Relational Empathy Measure (described below).Participants will complete a Semi-Structured Qualitative Interview to share their impressions of NAOMI and suggestions for its improvement.

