#### Statistical Analysis

NAOMI’s adherence to the core principles of MI will be assessed using the MITI coding scheme [111], a standard instrument for assessing MI fidelity. Two trained MITI coders (the primary and secondary) will code NAOMI’s utterances in the transcripts of its interactions with the study participants with MITI codes. The primary coder will code all transcripts with the second coder co-coding randomly selected 25% of transcripts to assess interrater agreement using the Krippendorff α statistic [124]. The quantitative assessment of NAOMI’s counseling skills based on the MITI-coded transcripts has 2 components: global scores and behavior counts. The global scores aim to characterize the overall quality of patient-counselor interaction and include 4 dimensions (Cultivating Change Talk, Softening Sustain Talk, Partnership, and Empathy). Behavior counts are evaluated by tallying instances of specific counselor behaviors, which can be grouped into 5 broad categories: questions, reflections, MI adherent behavior, MI nonadherent behavior, and neutral behaviors. The global scores and behavior counts will then be used to assess the level of NAOMI’s counseling skills according to the MITI manual.

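### The primary objective concerns a fully automated counselor, but every session is supervised with staff free to intervene, and no stated outcome counts those interventions or factually incorrect content

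*Protocol article*

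**What the plan says.** All references are to the Protocol article.

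- **Objective.** Goals of This Study sets the primary objective: to "explore the feasibility of conducting unscripted weight loss MI with a fully automated LLM-based AI counselor". The Conclusions again describe the product as fully automated.
- **Safeguard.** Limitations, Risks, and Mitigation Strategies names inappropriate and factually incorrect output as a risk, to be "mitigated by a study team member observing NAOMI’s interaction with every study participant and intervening should the interaction go awry". The same section names cohort effects as a limit on the results. It does not name supervision as one.
- **Visit.** In Study Visit (Textbox 1), participants interact with NAOMI "for at least 10 minutes but no more than 1 hour". The observer is not mentioned in these steps. All post-interaction questionnaires follow the session.
- **Fidelity scoring.** Under Statistical Analysis, two trained coders "will code NAOMI’s utterances in the transcripts of its interactions with the study participants with MITI codes". On coverage: "The primary coder will code all transcripts with the second coder co-coding randomly selected 25% of transcripts". On session-level scores: "The global scores aim to characterize the overall quality of patient-counselor interaction and include 4 dimensions".
- **Success criteria.** Study Hypotheses states that "NAOMI will achieve at least intermediate MI fidelity" and that "At least 80% of the last cohort of study participants will find NAOMI acceptable and usable". The third hypothesis is a positive shift in the motivational precursors.
- **Version choice.** System Versions and Training has stages 1 and 2 decide which approach is refined in stages 3 and 4.

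**The concern.** The condition tested is an AI counselor with a person standing by to step in. The conclusion sought is about an AI counselor alone, and the Introduction and Conclusions look ahead to use at any time and in any place. A session that needed a person to step in is the most direct evidence against full automation, and the stated criteria have no place for it.

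Three results are exposed:

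- **Fidelity and ratings.** An intervention redirects or ends the session. Later utterances, the global scores, the questionnaires and the rulers then describe an altered interaction.
- **The choice between approaches after stages 1 and 2.** A version that needed frequent intervention could be preferred to one that needed none, because this is not a stated criterion.
- **The later randomized trial.** The frequency of interventions and of incorrect content is basic safety information for planning it.

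Factual error is a separate gap. The article describes hallucinations as fluent and plausible, so participants cannot be relied on to notice them. The observer is the only stated means of detection, and the article describes no record of what the observer sees or does.

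**Working it through.** **Step 1: the plan's own figure.** Recruiting 50 to retain 40 implies attrition of 1 − 40/50 = 20%. Then 40/0.80 = 50, and 10/0.80 = 12.5 per cycle, which agrees with the stated 12-13. The 20% is back-calculated, not stated. These figures are consistent and not in dispute.

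**Step 2: is an intervention, or a factual error, counted anywhere?**

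| Place in the article | What it captures | Intervention counted? | Factual error counted? |
|---|---|---|---|
| Study Hypotheses, in Introduction and Discussion | Fidelity, acceptability and usability, motivational shift | No | No |
| Measures | Perceptions, rulers, usability, empathy, interview | No | No |
| Statistical Analysis | 4 global dimensions, 5 groups of behavior counts | No | No category listed |
| Textbox 1 | Visit steps | No | No |

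The MI nonadherent category could catch some inappropriate content. It is not a measure of accuracy.

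**Step 3: how likely is at least one intervention?** The article gives no rate, so the per-session rate q is an assumption. The formula is 1 − (1 − q)^n.

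| Assumed q | n = 10 (one version) | n = 40 (all completers) | Expected number in 40 |
|---|---|---|---|
| 5% | 1 − 0.95^10 = 40% | 87% | 2 |
| 10% | 1 − 0.90^10 = 65% | 98% | 4 |
| 20% | 1 − 0.80^10 = 89% | >99% | 8 |

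**Step 4: how far could handling move the 80% criterion?** Take 10 participants in the last cohort, so that 8/10 meets the criterion. Suppose k sessions were both rated favourably and intervened in.

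| Observed | k | Not counted as favourable | Excluded |
|---|---|---|---|
| 8/10 | 1 | 7/10 = 70%, misses | 7/9 = 78%, misses |
| 9/10 | 1 | 8/10 = 80%, meets | 8/9 = 89%, meets |
| 9/10 | 2 | 7/10 = 70%, misses | 7/8 = 88%, meets |
| 10/10 | 3 | 7/10 = 70%, misses | 7/7 = 100%, meets |

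One intervened session matters only when the result sits exactly on the line. From 9/10 it takes two, and then only under the stricter count. The table shows sensitivity to handling; it does not recommend the stricter count.

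**Step 5: what could the new outcome show?** If all 10 sessions of a version ran without intervention, the exact two-sided 95% lower limit for the intervention-free proportion would be 0.025^(1/10) = 69%. For 40 of 40 it would be 0.025^(1/40) = 91%, but that pools different versions. The interval belongs beside the count.

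No corresponding figure can be given for the fidelity result, because the article contains nothing from which to compute one.

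**The case against.** The strongest objection is that this argues from silence in a condensed article. The observer is openly disclosed. A definition of when a session has gone wrong, an observer log and coding rules for interrupted sessions may all sit in a full protocol or manual that is not shown. Much of this stands. A reader might infer that interventions are to be hidden, or that sessions are scored as though no person had been involved, but nothing in the article says so. The objection does not reach the published success criteria. The article sets these out itself, and they omit the event that bears most directly on the objective.

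Second, the coding rule gives partial protection. Only NAOMI's utterances are coded, so a staff member's words earn it no credit, and the utterance that prompted the intervention would normally remain in the transcript and be coded. This stands. What is left is indirect: the effect on everything that follows the intervention.

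Third, a reader might infer that the results are biased upward. Preventing worse content would favour NAOMI, but an interruption could also lower global scores and satisfaction. The documents do not settle the direction.

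Fourth, counting every intervened session as a failure would be wrong here. Acceptability is defined by participants' own views, so recoding a satisfied participant would change what is measured. Fidelity is not stated as a pass or fail per session, so failure has no defined meaning there. This stands, and the remedy avoids that rule.

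Finally, the 80% line belongs to a secondary objective, so the counts in the working illustrate the acceptability result and not the primary one.

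**Conclusion.** The point holds in this form: the fully automated objective and the staffed safeguard are not reconciled, and no stated criterion or measure counts interventions or factually incorrect content. Following the article as written, a conclusion about full automation, and the choice of version to refine, could rest partly on sessions in which a person stepped in. A bias in NAOMI's favour is plausible but not established, and its effect on fidelity cannot be sized from the article.

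The size depends on an intervention rate that the documents do not give. At an assumed 5% to 20% per session, at least one intervention in a cohort of 10 has a probability of 40% to 89%. The effect on the 80% criterion is limited to results at or near the line.

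This is a change that should be made, not a fatal flaw. It concerns measurement and reporting only; no view is taken on when staff should intervene.

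**What to change.** 1. Keep the observer, and log the time and reason of each intervention.
2. State completion of the session without staff intervention as a feasibility outcome. Report it as n/N with an exact 95% confidence interval for each version, and consider it when choosing the approach to refine.
3. Code MITI up to the first intervention, with an as-observed analysis alongside.
4. Report acceptability as participants rated it. Add a sensitivity analysis that excludes intervened sessions or shows them separately, without recoding them as failures.
5. Have the primary coder, who already codes every transcript, flag inappropriate or factually incorrect content whether or not the observer acted.
6. If interventions occur, limit the conclusion to supervised use.

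The cost is a short log per session and one extra flag in coding that is already planned. The feasibility result may look less favourable.

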### Conclusions

This study aims to explore the feasibility of developing NAOMI, an LLM-based Web app for fully automated MI-style weight loss counseling. If proven effective, LLM-based counseling agents have the potential to become a cost-effective approach for addressing the obesity epidemic at a public health level. They can also have a broad, transformative effect on the delivery of MI and other psychotherapeutic modalities helping to mitigate the key barriers to their widespread adoption and enabling just-in-time and on-demand counseling anywhere. Upon successful completion of this study, we will measure NAOMI’s efficacy in improving motivational precursors and actual lifestyle behaviors in a randomized clinical trial.

## Appendix

Multimedia Appendix 1 NIH peer-review report.

## Abbreviations

AI: artificial intelligence
CARE: Consultation and Relational Empathy
LLM: large language model
MI: motivational interviewing
MITI: Motivational Interviewing Treatment Integrity
NAOMI: Neural Agent for Obesity Motivational Interviewing
PCTQ-P: Perceptions of Computerized Therapy Questionnaire-Patient
